### Secondary hypotheses

- Patient satisfaction >6 points (on a scale of 1-10) is not significantly different between both groups
- Outpatient recovery after standard bariatric surgery with Healthdot monitoring is feasible based on evaluating recruitment rate (>60% of patients), adherence to protocol (>75% of patients), and the amount of missing data (<10%).
- False-positive notifications from the Healthdot system are lower than 10% of notifications per patient.
- Missed events (false negatives) i.e. there was no notification from the Healthdot system when the patient needed to go to the hospital, are lower than 5% of all notifications.
- Missed minor events occur less than five times per patient. Missed minor events are defined as when there was no notification from the Healthdot system and the patient contacted the hospital, but there was no need for the patient to visit the hospital.
- The outcome of patients who choose HD versus patients who were randomized to HD on a combined outcome measure as defined for the primary endpoint are the same.
- The number of adverse events is not significantly different in both groups.

|                                                                                                                    |              |                        |                  |                    |
|--------------------------------------------------------------------------------------------------------------------|--------------|------------------------|------------------|--------------------|
| Title: Clinical Investigation Plan                                                                                 |              | Author: [name] |                  | Philips restricted |
| DocID: ICBE-2-36455                                                                                                | Version: 3.0 | Date: 2020-DEC-08      | Status: Approved | Page: 21 of 44     |
| This document is based on Philips Research Template: Clinical Investigation Plan, ID: QR-TEM-57, Date: 2019-Mar-21 |              |                        |                  |                    |

- The amount of pain medication during day of surgery until evening in both groups is not significantly different.
- Clinical decisions made on basis of remote monitoring with the Healthdot system do not change in more than 5% of cases when information from a telephone consultation is also included in the decision making process.

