- Percentage of false positive of the positive notifications from the Healthdot system
- Total number of false positive of the positive notifications from the Healthdot system
- Total number of false negative notifications from the Healthdot system
- The outcome of patients who choose HD versus patients who were randomized to HD on a combined outcome measure as defined for the primary endpoint.
- To evaluate the outcome of patients who choose HD versus patients who were randomized to HD on a combined outcome measure as defined for the primary endpoint.
- Number of adverse events in both groups
- Amount of pain medication taken on the day of surgery in both groups
- Percentage of clinical decisions made based on the Healthdot system, that changed when information from a telephone consultation was also included.
- Patient and health professional satisfaction (on a scale from 1-10) for both the outpatient recovery after standard bariatric surgery group as the current recovery path group
- The costs involved with outpatient recovery after standard bariatric surgery supported by Healthdot and the cost involved with the current recovery path, in the period up to 7 days after surgery.

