#### *Discharge from hospital*

Patients in the outpatient recovery group will be released from hospital on the discretion of a nurse under supervision of a physician and return to their homes wearing the Healthdot. The Healthdot calculates and transmits heart rate, respiratory rate, posture and activity level. The physician will be able to view the values for these four parameters through a dashboard. On the dashboard, events with a heart rate above a pre-defined threshold will be flagged. A teleconsultation will be scheduled for the following morning (day 2). Before the teleconsultation, the Healthdot data will be interpreted by the physician who will then assess whether additional action is indicated. The decision based on Healthdot data is noted in the eCRF. After the teleconsultation, it is noted whether additional or

Met opmaak

Met opmaak

Tekstkleur: Au

Met opmaak

Met opmaak

|                                                                                                                    |              |                         |                  |                    |
|--------------------------------------------------------------------------------------------------------------------|--------------|-------------------------|------------------|--------------------|
| Title: Clinical Investigation Plan                                                                                 |              | Author: [name] |                  | Philips restricted |
| DocID: ICBE-2-36455                                                                                                | Version: 3.0 | Date: 2020-DEC-08       | Status: Approved | Page: 25 of 44     |
| This document is based on Philips Research Template: Clinical Investigation Plan, ID: QR-TEM-57, Date: 2019-Mar-21 |              |                         |                  |                    |

different decisions are made about the treatment based on the additional information from the teleconsultation.

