## Statistical design

This study is primarily designed to test for non-inferiority of outpatient recovery compared to regular treatment for bariatric surgery. The outcome measure that we will use for the analysis is a combined measure, based on the following:

- Mortality
- Severe postoperative complications (Clavien-Dindo IIIb or higher)
- Readmission (at least one night in hospital)
- Mild complications (Clavien-Dindo II and IIIa)
- Prolonged length of stay (3 days or more in hospital)

within 30 days after primary surgery.

We choose to use this combined outcome measure since it is in line with other surgical studies [5] making it comparable to literature.

I current practice at Catharina Hospital, Eindhoven, 95% of all bariatric surgery patients do not have any of these events which is considered the textbook outcome here.

We set the following null and alternative hypotheses for proving non-inferiority:

$H_0: p_{\text{regular}} - p_{\text{outpatient}} \geq \Delta$

$H_1: p_{\text{regular}} - p_{\text{outpatient}} < \Delta$

Where  $p_{\text{regular}}$  is the textbook outcome proportion in the regular treatment group, and  $p_{\text{outpatient}}$  is the textbook outcome proportion in the outpatient recovery group. We will use a non-inferiority margin ( $\Delta$ ) of 7%, which is deemed clinically significant by the Principal Investigator. This is also justified by a previous study where the average textbook outcome across bariatric surgery patients in the Netherlands was 88,7% [5] which helps to derive a non-inferiority margin of around 7% to the one seen at Catharina Hospital. We will use an uncorrected chi-squared statistic. Based on the sample size calculation done below an p value of 0.05 will be considered statistically significant. For the interim analysis an alpha correction for multiple testings is applied and a p value of 0.025 will be considered statistically significant.

The secondary endpoints will be analysed statistically in analogy to the primary endpoint by uncorrected chi-squared statistic where deemed appropriate.

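### The 5% limit on changed decisions is not tied to how often action is needed, so if few patients need action a monitor that shows nothing would probably meet it

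*Protocol*

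**What the plan says.** Under Secondary hypotheses in section 5, the protocol accepts the hypothesis if "Clinical decisions made on basis of remote monitoring with the Healthdot system do not change in more than 5% of cases" when information from the call is added. Section 6.1 (General) defines the matching endpoint as "Percentage of clinical decisions made based on the Healthdot system, that changed when information from a telephone consultation was also included". Both are overall percentages. Neither separates a change towards action from a change away from it.

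The procedure is in section 6.4, Discharge from hospital. On the morning of day 2, "Before the teleconsultation, the Healthdot data will be interpreted by the physician who will then assess whether additional action is indicated". Then "The decision based on Healthdot data is noted in the eCRF", and after the call the physician notes whether additional or different treatment decisions followed. The term action is not defined, and no expected rate of action is given.

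The closest base rate is in section 7, Statistical design, which states for current practice that "95% of all bariatric surgery patients do not have any of these events which is considered the textbook outcome here". That figure covers 30 days and a composite of death, complications, readmission and prolonged stay.

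Section 5 states that the secondary hypotheses will be accepted or rejected on the results, and that claims may be derived from them.

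**The concern.** An overall change rate mixes two things: how often action is needed, and how well the pre-call decision anticipates that need. If nearly everyone needs no action, a physician looking at an empty dashboard would decide on no action each time and would rarely be contradicted by the call. The change rate would be low even though the monitor contributed nothing.

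The stake is the meaning of a pass. Because section 5 allows claims to be built on secondary hypotheses, meeting the 5% limit could be read as evidence that Healthdot data identify patients who need action, when every such patient might have been found only by the call.

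**Working it through.** **Inputs from the protocol**
- Limit: not more than 5% of cases changed (section 5, Secondary hypotheses).
- Outpatients: 100 (section 7, Sample size).
- Base-rate proxy: 5% with a composite event over 30 days, from the 95% in section 7, Statistical design; 4% if the planning proportion of 0.96 is used.

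**The plan's own figure.** The protocol gives no error rates for this criterion. The group size it relies on is set by the primary endpoint and reproduces with a one-sided alpha of 0.05 and power of 0.80:

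n = (1.645 + 0.842)² × 2 × 0.96 × 0.04 / 0.07² ≈ 97, rounded up to 100 by the sponsor.

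**Assumptions**
- One paired decision per outpatient, on day 2, so n = 100 and a pass means 5 or fewer changes.
- q, the share of patients for whom action is decided after the call, is not in the protocol. A range of 1% to 10% is shown.
- The post-call decision is treated as the reference.

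**Change rate.** For a monitor with sensitivity s and false-alarm rate f:

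c = q(1 − s) + (1 − q)f

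A blank monitor has s = 0 and f = 0, so c = q. The chance of a pass is P(X ≤ 5) with X ~ Binomial(100, c).

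**Blank monitor**

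| q | P(pass) |
|---|---|
| 1% | 0.9995 |
| 2% | 0.985 |
| 3% | 0.919 |
| 4% | 0.788 |
| 5% | 0.616 |
| 7% | 0.291 |
| 10% | 0.058 |

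**Comparison at low q.** At q = 4%, take s = 0.90 and f = 0.05:

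c = 0.04 × 0.10 + 0.96 × 0.05 = 0.004 + 0.048 = 0.052, P(pass) = 0.580.

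The blank monitor passes with 0.788. False alarms among the 96% who need no action cost the sensitive monitor more than missing everyone costs the blank one.

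**Comparison at moderate q.** At q = 10%, take s = 0.90 and f = 0.01:

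c = 0.10 × 0.10 + 0.90 × 0.01 = 0.019, P(pass) = 0.988.

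The blank monitor passes with 0.058. Here the rule separates the two devices.

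**Do the other criteria fill the gap?** The false-positive and missed-event limits in section 5 both use notifications as the denominator. Neither gives the proportion detected among patients who needed action, and with no notifications both are undefined.

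**The case against.** The strongest defence is that the objective is to compare decisions made with and without the call, that is, to learn what the call adds. An overall change rate answers that question directly, and device performance has its own false-positive and missed-event criteria. This stands as a reason to keep the rate as a descriptive measure. It does not support using the rate as evidence about the Healthdot, because those other criteria do not measure detection among patients needing action either.

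Several stronger readings are tempting, and the documents do not support them:
- A reader might infer that about 95% of patients need no action on day 2. The protocol does not say so: its 95% is a 30-day textbook-outcome rate. Day-2 events should be rarer than 30-day events, but the undefined action may include small steps that are not composite events, so q could lie on either side of 5%.
- A reader might infer that a blank monitor is certain to pass. It passes with 0.62 at q = 5% and 0.06 at q = 10%.
- A reader might infer that the result depends only on q and never on the device. The formula contains s and f, and at q = 10% the rule discriminates well.
- A reader might extend the criticism to the limit on missed minor events ("Missed minor events occur less than five times per patient"). That would need a rate of patient calls, which the protocol does not give.

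Two further points stand in part. The protocol speaks of cases and decisions in general and allows telephone consultations on days 3 to 8, so one pair per outpatient is a reading of the day-2 procedure rather than an explicit rule. And section 5 says only that claims may be derived, while trial success rests on the primary endpoint; nothing says that the call would be dropped.

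**Conclusion.** The concern holds conditionally. The protocol fixes an acceptance rule on an overall change rate without relating the 5% limit to how often action is needed. If q is 1% to 4% with about 100 paired day-2 decisions, a monitor that shows nothing meets the limit with probability 0.9995 to 0.79. At q = 4% it does so more often than a monitor with 90% sensitivity and 5% false alarms (0.79 against 0.58). In that range a pass does not show that Healthdot data identify the patients who need action. At around q = 10% the rule is informative.

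The conclusion rests on q, which is assumed, and on one paired decision per outpatient. It affects one secondary hypothesis and any claim drawn from it, not the primary analysis.

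**What to change.** Change the hypothesis in section 5 and the matching endpoint in section 6.1:
- Keep the overall change rate as a descriptive measure of what the call adds.
- Report the pre-call and post-call decisions as a 2×2 table, split by direction of change.
- Base any conclusion or claim about the Healthdot on two proportions with exact 95% intervals: among patients with action after the call, the share already marked for action before it; among those without, the share already marked for no action.

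The cost is wording only, since section 6.4 already has the Healthdot-based decision and any change after the call noted.

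There are two limits. The detection estimate will be wide: at q = 5% about 100 × 0.05 = 5 patients would need action, and even 5 of 5 detected gives an exact two-sided 95% lower limit of 0.025^(1/5) = 0.478. And the post-call decision is not an independent reference, because the physician has already seen the Healthdot data. Both should be stated with the result.

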### Claims and intended performance

In this investigation it will be tested if the Healthdot is suitable as a tool for out of hospital monitoring enabling a change in standard of care workflow for patients after surgery. Depending on the outcome claims may be derived from the primary and secondary hypothesis.

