| Claims                                                                                                                                     | 
Will you obtain regulatory (FDA, CE) approval for a new product or service, a new indication, or a new marketing claim?
 
 Yes    No
 
If YES, in what countries will the claims be registered?
 
 Netherlands    USA    Germany    China
 
 India    Belgium    UK    Kenya
 
 Other:
 
Have you developed a list of claims that you would like to assert for your product or service?    Yes    No
 |
| External Medical Ethics Committee Approval

Note: if your document is not in English or Dutch, include an English translation | 
 Not Required (not a local/state/country requirement)
 
 Required (apply for it AFTER ICBE approval)
 
 Approval already obtained (upload for review by ICBE)
 
 REC Review is waived (upload review waiver)
 
 REC has waived requirement for informed consent (upload waiver)
 
 Check this box if more than one REC is involved in this study and identify them:
                                                                                                                                                                                                                                     |

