- Patient and health professional satisfaction (on a scale from 1-10) for outpatient recovery after standard bariatric surgery with the Healthdot are equal or higher than for current treatment.
- The costs involved with outpatient recovery after standard bariatric surgery supported by Healthdot is less than the cost involved with the current recovery path, in the period up to 7 days after surgery.
- The usability of the visualization of Healthdot data on the Guardian dashboard is scored good (at least 4 out of 5).

These hypotheses will be accepted or rejected based on the outcome of this clinical investigation.

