### Pass/fail criteria

The study is considered successful if the primary endpoint is addressed and the non-inferiority of outpatient recovery compared to regular treatment for bariatric surgery can be concluded.

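### Claims may be drawn, once the outcome is known, from any of 12 accept-or-reject secondary hypotheses, with no preset claims list and no condition that the primary succeeds

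*Protocol*

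**What the plan says.** All of this is in the protocol.

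- **Section 5, Secondary hypotheses.** Twelve bullets, closed by: "These hypotheses will be accepted or rejected based on the outcome of this clinical investigation".
- **Section 5, Claims and intended performance.** "Depending on the outcome claims may be derived from the primary and secondary hypothesis".
- **Section 1, Claims.** To the template question "Will you obtain regulatory (FDA, CE) approval for a new product or service, a new indication, or a new marketing claim" the answer is Yes. To "Have you developed a list of claims that you would like to assert for your product or service" the answer is No.
- **Section 7, Statistical design.** For the primary test, "an p value of 0.05 will be considered statistically significant". The only adjustment for multiplicity is at the interim: "For the interim analysis an alpha correction for multiple testings is applied and a p value of 0.025 will be considered statistically significant". For the rest: "The secondary endpoints will be analysed statistically in analogy to the primary endpoint by uncorrected chi-squared statistic where deemed appropriate".
- **Section 7, Pass/fail criteria.** "The study is considered successful if the primary endpoint is addressed" and non-inferiority can be concluded. The rule concerns the study's success and does not mention claims.

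**The concern.** The secondary hypotheses are not presented as exploratory. Each is to be decided, and each is named as a possible source of a claim. Which of them will be used is left open until the results are in. Nothing makes a secondary claim depend on non-inferiority having been shown for the primary endpoint.

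The trial could thus miss its primary objective and still yield a claim on satisfaction, cost, notification accuracy, feasibility or dashboard usability. Such a claim would be chosen because that result came out well. A reader would take the trial's 5% error rate as applying to it, and it would not.

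**Working it through.** **1. The level in the plan.** The protocol gives no familywise error figure, so the figure to reproduce is the sample size in Section 7: expected proportion 0.96, margin 0.07, power 0.80, alpha 0.05, giving 97 per group.

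n = 2p(1 − p)(z_alpha + z_power)² / margin²

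- One-sided 0.05: 2 × 0.96 × 0.04 / 0.0049 = 15.67, and (1.645 + 0.842)² = 6.18. The product is 96.9, so n = 97, which matches.
- One-sided 0.025: (1.960 + 0.842)² = 7.85. The product is 123.02, so n = 124, which does not match.

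The primary level is therefore one-sided 0.05. If the secondary endpoints are handled by analogy, this is the level they would inherit. That is an inference, since no level is stated for them.

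**2. What kind of statement each hypothesis is.** Sorting the 12 bullets by wording:

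| Type | Number | Which |
|---|---|---|
| Directional group comparison | 2 | patient and professional satisfaction equal or higher; lower cost |
| No difference, or the same | 4 | satisfaction above 6; chosen versus randomized Healthdot; adverse events; pain medication |
| Fixed threshold, no test stated | 6 | feasibility; false positives; missed events; missed minor events; changed decisions; dashboard usability |

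The satisfaction bullet in the first row covers two sets of respondents, so that row contains two or three tests.

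**3. Directional comparisons.** Assume each is tested at 0.05, the tests are independent, and every null is true. Then P(at least one false claim) = 1 − 0.95^k.

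- k = 2: 1 − 0.9025 = 9.8%
- k = 3: 1 − 0.8574 = 14.3%

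Positive correlation lowers these figures towards 5%. Whatever the dependence, three tests cannot exceed 3 × 0.05 = 15%.

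**4. No-difference hypotheses.** As worded, these are supported by a non-significant result, so a false claim is a type II error. As an illustration, take 100 per group, a two-sided chi-squared test at 0.05, and assumed true rates of 95% and 88%, whose mean p̄ is 0.915:

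power = Φ{[√n·|p1 − p2| − 1.96·√(2p̄(1 − p̄))] / √(p1(1 − p1) + p2(1 − p2))} = Φ{[0.700 − 1.96 × 0.3944] / 0.3913} = Φ(−0.187) = 0.426

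The real difference of 7 points would be declared absent 57% of the time. Under other assumed rates the figure is 73% (95% versus 90%), 49% (90% versus 80%) and 20% (90% versus 75%). The chosen-versus-randomized comparison lies within the outpatient group alone, so it has fewer patients than this illustration.

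**5. Threshold hypotheses.** With no test stated, the natural reading is that the observed value is compared with the limit. For the limit of 5% changed decisions, assume 100 decisions and a pass if 5 or fewer change. The binomial probability of passing is 44% when the true rate is 6% and 18% when it is 8%. No error rate is fixed in advance for any of the six.

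**6. Is there a gate?** Comparing the claims sentence with the pass/fail rule shows none. The first names primary and secondary hypotheses together as sources of claims. The second defines success by the primary endpoint but does not say that a claim requires success.

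**The case against.** Multiplicity details commonly sit in a statistical analysis plan, and none is shown here. The hypotheses are fixed in advance, many with numeric limits, so the claims sentence may mean only that a claim follows if its listed hypothesis is supported. The box on claims may record that no list exists yet, which is not a plan to choose afterwards. No sentence says that a claim may be made after the primary fails.

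Part of this stands. The absence of a hierarchy or alpha split is no finding in itself, and the documents do not show an intention to select. But the protocol does more than stay silent. It states a rule that opens every hypothesis to claims according to outcome and gives each one decision status. A later analysis plan could add levels and an order, yet that permission would remain as written. Nor does fixing the hypotheses in advance limit how many of them may feed a claim.

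A reader might go further, multiply 12 hypotheses by a 0.05 level, and conclude that a false claim is likely: 1 − 0.95^12 = 46%. The documents do not support this. The 0.05 level is not stated for secondary endpoints. Four hypotheses are accepted on non-significance and six have no test, so alpha inflation is not how they go wrong. Even this figure, which needs independence and all 12 nulls true at once, is below one half.

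**Conclusion.** The point holds as a defect in the claims rule. The nominal 5% does not extend to the set of claims the protocol permits. For the directional comparisons, the chance of at least one false claim is about 10% with two tests and 14% with three. That rests on testing at 0.05 each (inferred from Section 7), independence and true nulls. It also assumes that the equal-or-higher satisfaction hypothesis is judged by a significance test; if it is judged on the observed means, it too has no controlled error.

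For the other ten hypotheses there is no controlled false-claim rate to quote. The figures under assumed rates show only that wrong acceptance can be common. The primary analysis and the sample size are not affected. This is a cheap improvement.

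**What to change.** In Section 5, Claims and intended performance, state that confirmatory claims are derived from the primary hypothesis only, and that secondary hypotheses are reported as estimates with 95% confidence intervals and support no claim on their own. In the closing sentence of the secondary hypotheses, replace the accept-or-reject wording with a statement that the results will be described. This covers all 12 whatever their type of error. A Bonferroni split would not: it does nothing for untested thresholds and makes false acceptance of no difference more likely.

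If the sponsor wants a secondary claim, name it now. Give it a directional or margin-based confidence-interval criterion in place of a non-significance rule, and test it in a fixed order only after the primary has succeeded. Satisfaction could not enter such a sequence as it stands: it appears in two forms and neither has a margin.

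The cost is a few sentences in Sections 5 and 7, with no added patients or data. The downside is that fewer secondary results can be worded as claims.
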